### Study procedures

Study participants will undergo several clinical and laboratory assessments, complete various questionnaires and participate in qualitative interviews, as detailed in the schedule of activities (SoA) (
Table 2).

**Table 2. T2:** IMPALA Trial Schedule of Activities.

Phase	Screening period ^ a ^		Optional OLI ^ b ^		Initiation (Months)	Maintenance Phase (Months)															
Period	SCR 1	SCR 2 ^ a ^	Baseline	1	2	3	4	6	8	9	10	12	14	15	16	18	20	21	22	24 ^ c ^	Unscheduled Visit ^ t ^
**Visit Window (days)**			**±8**	**±7**																	
Study visits – vary by arm, activities listed below only apply if the participant has a visit scheduled in line with their randomization arm																					
CAB LA + RPV LA			X	X	X		X	X	X		X	X	X		X	X	X		X	X	X
cART	X	(X) ^u^	X			X		X		X		X		X		X		X		X	
Clinical assessments and procedures																					
Informed consent / assessment of understanding	X																				
Administration of oral CAB and RPV			X ^ b ^																		
Administration of IM CAB/ RPV ^ d ^				X	X		X	X	X		X	X	X		X	X	X		X	X	X
Chest Xray, ECG	X																				
Assessment of eligibility	X	(X) ^u^																			
Medical history and demographics	X																				
Adherence assessment ^ e ^	X	(X) ^u^	X	X		X		X		X		X		X		X		X		X	X
Con-meds	X	X	X	X	X	X	X	X	X	X	X	X	X	X	X	X	X	X	X	X	X
Vital Signs	X	X	X	X	X	X	X	X				X				X				X	X
Physical examination	X		X					X				X				X				X	
ISR assessment				X	X		X	X	X		X	X	X		X	X	X		X	X	X
AE assessment ^ f ^	X	X	X	X	X	X	X	X	X	X	X	X	X	X	X	X	X	X	X	X	X
Weight and appetites	X		X					X				X ^ s ^				X				X ^ s ^	
Height			X																		
EuroQoL-SD-SL			X					X				X								X	
MOS-HIV			X					X				X								X	
HIVTSQs			X					X													
HIVTSQc												X								X	
Treatment preference												X								X	
Medical resource utilization and patient-related outcomes																					
MRU			X									X ^ g ^				X					
In-depth interviews ^ h ^			X					X				X									
OLI questionnaire (LA arm only)			X																		
Blood and urine tests																					
HIV-1 RNA ^ i, j ^	X	(X) ^ iu^	X		X ^ k ^	X ^ l ^		X	X ^ k ^	X ^ l ^		X				X				X	
CD4+ count	X		X					X				X				X				X	
Hepatitis B serology (HBcAb, HBsAg, HBsAb)	X											X ^ r ^								X ^ r ^	
Hepatitis C serology (HCV Ab)	X																				
CBC, Biochemistry ^ m ^	X		X		X	X	X ^ q ^	X				X				X				X	
HbA1c, fasting lipids			X									X								X	
Urine HCG ^ n ^	X	(X) ^u^	X	X	X	X	X	X	X	X	X	X	X	X	X	X	X	X	X	X	X
Urine dipstick (protein, glucose)			X					X				X				X				X	
Store PBMC or whole blood ^ o ^			X																		
Store plasma ^ p ^	X		X		X ^ k ^	X ^ l ^		X	X ^ k ^	X ^ l ^		X				X				X	

**Abbreviations:** AE = adverse event; ART= antiretroviral therapy; CAB= cabotegravir; CBC = complete blood count; Con-meds = concomitant medications; ECG= electrocardiogram; FGDs = focus group discussions; HbA1c = hemoglobin A1c; HBcAb = hepatitis B core antibody; HBsAg = hepatitis B surface antigen; HBsAb = hepatitis B surface antibody; HCG= human chorionic gonadotrophin; HCVcAb = hepatitis C core antibody; HIVTSQc= HIV Treatment Satisfaction Questionnaire- change version; HIVTSQs= HIV Treatment Satisfaction Questionnaire- status version; IM= intramuscular; ISR= injection site reactions; LA=long acting; OLI=oral lead-in; PBMC= peripheral blood mononuclear cells; RPV=rilpivirine; SCR = screening.
**Footnotes:**
a. Screening visit 2 is only required if HIV-1 VL ≥200 at screening visit 1 or duration of virologic suppression (HIV-1 VL <200 c/mL) has not reached 3 months. Once a participant is confirmed as virologically suppressed (<200 c/mL), and duration is ≥3 months then randomization should occur within 2 weeks. The screening period must be completed within 4 months. a. One month of oral CAB and RPV (OLI) or continue daily oral ART (DTI) prior to first injections of CAB LA + RPV LA at month 1. b. Perform Month 24 assessments in all participants who withdraw from study intervention prematurely (if participant is willing), and scheduled assessments off the study intervention should be continued up to the Month 24 visit as specified in Section 7.1, Discontinuation of Study Intervention. c. For participants with BMI ≥30 a longer needle should be used as per product administration instructions. d. Adherence assessment and tablet count only in participants receiving daily oral ART, or oral lead-in/bridging treatment in CAB LA + RPV LA group. e. Clinical AEs will be captured from the time of screening. Laboratory abnormalities will not be recorded/reported as AEs till after the baseline visit. f. Detailed healthcare resource data survey to be performed at Month 12 visit, at selected sites only g. From a purposively selected sample at selected sites. h. HIV-1 VL can be repeated on one additional occasion after screening visit 1 if it is still ≥200 c/mL. i. Additional HIV-1 VL testing is performed after 4 (3–6) weeks in participants with VL ≥200 c/mL in CAB LA + RPV LA group; additional plasma sample stored (for batched, blinded viral load testing) after 4 (3–6) weeks in participants with VL ≥200 c/mL in the cART arm; and additional viral load after 12 (10–14) weeks in participants with viral load ≥1000 c/mL in the cART arm; reflex resistance testing is performed on stored plasma sample in participants with VL ≥200 c/mL in the CAB LA + RPV LA group, or ≥1000 c/mL in the cART group. (See also Section 8.1.1.2 for an alternative threshold for testing and definition of virologic failure in the cART group) Pregnant participants in the CAB LA + RPV LA arm who continue the study should have viral load monitoring frequency increased to every 2 months aligned with CAB LA + RPV LA Q2M injection visits during pregnancy and for 6 months following delivery or more frequently as per treating physician preference. Repeat HIV-1 VL testing should be performed after 2–3 weeks in pregnant participants with VL ≥50 c/mL. j. CAB LA + RPV LA arm only k. cART arm only l. Complete blood count: hemoglobin, total white cell count and differential, neutrophil count, platelets. Biochemistry: creatinine, sodium, potassium, alanine transaminase, alkaline phosphatase, total bilirubin, aspartate aminotransferase (at screening only). For individuals switched from NNRTI to dolutegravir during the screening period national guidelines should be followed regarding glycemic monitoring before and after switch. m. Only required for females of reproductive potential n. PBMC stored for baseline archived genotypic drug resistance testing. o. One large size (8–10 mL) EDTA sample stored at the following time-points: at screening, baseline visit, all visits where HIV VL is performed, and each visit where the blood is taken for confirmation of viral load rebound (for additional resistance testing, pharmacokinetic analysis, immune or biomarker tests; both arms); at 1, 3, 6, and 12 months following cessation of CAB LA + RPV LA in participants who develop TB (for drug levels; CAB LA + RPV LA group only); at 1
^st^, 2
^nd^, and 3
^rd^ trimester and postpartum in pregnant women (for drug levels; in those continuing CAB LA + RPV LA only); in individuals consenting to peak drug level measurement, at 1 week (±1 day) post injection at Month 4, Month 6, Month 10, Month 16, Month 22, where feasible. p. Liver function tests (total bilirubin, alanine transaminase, alkaline phosphatase) should be repeated in those in the CAB LA + RPV LA arm who have a positive HBcAb during screening. q. Hepatitis B surface antigen (HBsAg) - only in those in the intervention arm who had positive hepatitis B core antibody (HBcAb) at screening. r. Appetite will be evaluated only at Month 12 and M-nth 24. s. An unscheduled visit to re-initiate CAB LA + RPV LA may occur between two 2-month interval visits following discontinuation due to pregnancy or TB. All the assessments at this visit are similar to those performed at the Month 1 initiation visit. A viral load measurement will need to be taken at the prior visit one month earlier and reviewed at this re-initiation visit to ensure viral suppression at re-initiation. t. “(X)” marks assessment/activity that has an impact on the inclusion/exclusion criteria of the participant.

### Laboratory procedures

Blood samples are collected for the following tests per the SoA (
Table 2): haematology (complete blood count), CD4+ T cell count, serum chemistry (sodium, potassium, creatinine, liver function tests [LFTs] including alanine transaminase (ALT), aspartate aminotransferase (AST), total bilirubin, alkaline phosphatase (ALP)), a metabolic profile (haemoglobin A1c (HbA1c), fasting cholesterol, fasting triglycerides) and random urine sample for urinalysis. For participants in the CAB LA + RPV LA arm with a positive screening hepatitis B core antibody (HBcAb), repeat LFTs are required at the Month 4 visit. In the control arm, individuals who are switched from NNRTI to DTG during the screening period undergo additional glucose monitoring if required by national guidelines.

The laboratory results are reviewed by the investigator who documents the review and records any clinically relevant changes occurring during the study in the Adverse event (AE) log. Urine pregnancy tests are performed at all study visits for female participants of reproductive potential.

For efficacy assessments, participants in both groups have routine HIV-1 VL monitoring at baseline and Months 6, 12, 18, and 24. Participants in the CAB LA + RPV LA Q2M arm also have HIV-1 VL monitoring at Months 2 and 8, and those in the oral ART control arm have additional HIV-1 VL monitoring at Months 3 and 9.

### Clinical assessment

Participants have vital signs including respiratory rate, heart rate and blood pressure measured at each visit during the screening period and the first six months of the study. These measurements are then taken again at Months 12, 18 and 24. Height is measured at the baseline visit to enable body mass index (BMI) calculations, and weight is measured at screening, baseline and Months 6, 12, 18 and 24.

At every visit, participants are assessed for any interim AEs. All clinical AEs are recorded from the first screening visit onwards, while asymptomatic laboratory AEs are reported from after baseline onwards. Post-injection reactions are considered AEs of special interest and will be recorded as such.

### Qualitative methods sub-study

As shown in the SoA, participants complete questionnaires on quality of life
^
18,
19
^ and treatment satisfaction
^
20
^ at baseline and at Months 6, 12 and 24. Additionally, participants in the CAB LA + RPV LA arm answer a single question regarding treatment preference at Months 12 and 24. All participants are asked to complete a brief questionnaire about medical resource utilisation at months 12 and 18 to support health economic analysis. A brief questionnaire regarding the choice of OLI versus DTI will be administered at baseline to all participants randomised to the CAB LA + RPV LA arm.

In-depth interviews are conducted with a subset of 10–20 individuals from both Uganda and South Africa, at baseline, Month 6, and Month 12. Participants provide separate consent to participant in this qualitative sub-study. Additionally, up to 15 individuals who experience virological failure in the CAB LA + RPV LA arm will be approached to participate in a single in-depth interview, using a separate participant information sheet and consent form.

### Pregnancy

All initial reports of pregnancy in female participants or partners of male participants must be reported to the sponsor by the study-site personnel within 24 hours of their knowledge of the event using the appropriate pregnancy notification form. Abnormal pregnancy outcomes (e.g., spontaneous abortion, foetal death, stillbirth, congenital anomalies, ectopic pregnancy) are considered Serious Adverse Events (SAEs) and must be reported using a SAE reporting form. Any participant from the CAB LA + RPV LA arm who becomes pregnant will be permitted to continue the study product after providing separate informed consent. Plasma samples for pharmacokinetic (PK) analyses will be taken from pregnant participants, for evaluation of CAB and RPV concentrations. The frequency of HIV-1 VL monitoring will increase to 2-monthly for the duration of the pregnancy, and all infants’ HIV-1 test results will be followed up.

### Measurement of CAB LA and RPV LA concentrations

Drug concentration measurements within the study may be useful in understanding how drug exposures vary according to demographic or anthropometric factors (such as sex, BMI or pregnancy), and for determining how drug concentrations impact treatment outcomes. Samples for measuring of drug levels are collected in various scenarios as outlined in the SoA, including during pregnancy, tuberculosis treatment, treatment overdose, inadvertent intravenous administration and virological failure. Peak (1 week post injection) and trough drug levels (collected pre-injection) will also be measured from stored plasma samples in a subgroup of participants.

### Sample size calculation

Assuming a true 78% virologic response rate in each group, a non-inferiority margin of -10%, and a 2-sided 5% significance level (one-sided 2.5% significance level), this study requires 270 participants per treatment group to provide 80% power to test the hypothesis of noninferiority of CAB LA + RPV LA Q2M vs. daily oral ART. Should non-inferiority be demonstrated, this sample size also provides 80% power to declare superiority of CAB LA + RPV LA Q2M compared with daily oral ART if the difference in virologic response between the treatment arms is 10% (83% CAB LA + RPV LA Q2M vs. 73% daily oral ART).

In addition, this sample size provides at least 80% power for the key secondary non-inferiority hypothesis for virologic failure, with a 2-sided 5% significance level, non-inferiority margin of 4% and assumed virologic failures rates of 4% in CAB LA + RPV LA and 6% in daily oral ART.

### Objectives and endpoints

The objectives and endpoints of the Study are shown in
Table 3.

**Table 3. T3:** Study Objectives and Endpoints.

Objectives	Endpoints
Primary:	
To demonstrate the non-inferior efficacy of switching to every 2 months (Q2M) intramuscular (IM) injection of cabotegravir (CAB) long-acting (LA) plus rilpivirine (RPV) LA compared with continuation of daily oral ART over 12 months in people living with HIV-1 (PLHIV1) with a history of sub-optimal ART adherence or engagement in care	• Proportion with plasma HIV-1 viral load (VL) <50 c/mL at 12 months (by Food and Drug Administration [FDA] snapshot algorithm)
Secondary:	
To demonstrate the antiviral activity and the impact on retention in HIV care of switching to Q2M CAB LA + RPV LA compared with continuation of daily oral ART over 12 and 24 months in PLHIV1 with a history of sub-optimal ART adherence or engagement in care	• Proportion with confirmed virologic failure (CVF) [plasma HIV-1 VL ≥200 c/mL on 2 consecutive occasions] at 12 and 24 months • Proportion with LTFU [>4 weeks elapsed since their last missed appointment] at 12 and 24 months • Proportion with plasma HIV-1 VL <200 c/mL at 12 months by FDA snapshot algorithm • Proportion with virologic response [plasma HIV-1 VL <50 c/mL] at 24 months by FDA snapshot algorithm • Proportion with virologic non-response [plasma HIV-1 VL ≥50 c/mL] at 12 and 24 months by FDA snapshot algorithm
To demonstrate the immunological activity of switching to Q2M CAB LA + RPV LA compared with continuation of daily oral ART over 12 and 24 months in PLHIV1 with a history of sub-optimal ART adherence or engagement in care	• Change in CD4+ T cell count from baseline (12 and 24 months) • Incidence of HIV disease progression (HIV/AIDS-related hospitalizations, illness, or deaths) (through 24 months)
To evaluate the safety and tolerability of switching to Q2M CAB LA + RPV LA compared to continuation of daily oral ART	• Incidence of adverse events through 12 and 24 months • Incidence of adverse events, Grade 3 and 4 (through 12 and 24 months) excluding injection site reactions (ISRs) • Frequency of ISRs of any grade
To assess genotypic viral resistance in participants experiencing protocol-defined CVF (confirmed plasma HIV-1 RNA ≥200 c/mL on 2 consecutive tests) and its impact on future treatment options including proportion who resuppress on dolutegravir	• Frequency of emergence of new integrase strand transfer inhibitor (INSTI) and non-nucleoside reverse transcriptase inhibitor (NNRTI) drug resistance mutations in those who develop virologic failure (through 12 and 24 months)
Exploratory	
To evaluate the effect of Q2M CAB LA + RPV LA on health-related quality of life	• Change from baseline in EQ-5D-5L at Month 12 and Month 24 • Change from baseline in MOS-HIV at Month 12 and Month 24 • Quality of life outcomes of in-depth interviews
To assess treatment satisfaction	• For participants in the CAB LA + RPV LA group, change from baseline in HIVTSQ scores at Month 6, Month 12 and Month 24
To assess preference for Q2M CAB LA + RPV LA compared to daily oral ART	• For participants randomized to the CAB LA + RPV LA group, preference for CAB LA + RPV LA compared to daily oral ART regimen at Month 12 and Month 24 using a single dichotomous preference question
To measure participants' medical resource utilization under Q2M CAB LA + RPV LA compared to daily oral ART	• Medical resource utilization over 24 months • Clinic/hospital attendances • Rates of opportunistic infections and other illnesses
To assess programmatic acceptability of Q2M CAB LA + RPV LA	• Thematic analysis of data from interviews participants, healthcare workers and key stakeholders
To evaluate adherence to treatment	• Self-reported adherence and pill count for daily oral ART and delayed/missed injections for CAB LA + RPV LA
To evaluate drug levels	• Plasma concentrations of CAB LA and RPV LA

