**Figure 1. f1:**
[figure not shown]
Schematic overview of the IMPALA Trial.

The study target is 540 participants (270 participants per intervention group). Participants were recruited across sites from three countries (Uganda, Kenya and South Africa). The list of study sites is available from the trial registration on clinicaltrials.org. The trial population comprises participants with no significant laboratory abnormalities at screening, negative hepatitis B status, willing to adhere to suitable methods of contraception and with no known history of non-nucleoside reverse transcriptase inhibitor (NNRTI) and/or integrase strand transfer inhibitor (INSTI) resistance. The detailed list of inclusion and exclusion criteria is shown in
Table 1.

**Table 1. T1:** IMPALA Trial Inclusion and Exclusion Criteria.

IMPALA Trial Inclusion and Exclusion Criteria	
Inclusion Criteria	
**1.**	18 years of age and above.
**2.**	HIV-1 infection confirmed in clinic records or by study team.
**3.**	Virologically suppressed (HIV VL <200 copies/mL) for ≥3 months prior to randomization visit
**4.**	Is on a first-line oral regimen of 2NRTI + DTG
**5.**	Is identified as a participant with a history of, or at risk of, sub-optimal ART adherence or engagement in care based on one or more of the following criteria: a. Documented detectable HIV-1 viral load (>1000 c/mL) on all-oral ART (EFV/NVP or DTG-based) in the prior 2 years despite being ART-experienced for >3 months. b. History of being lost to follow-up from care (>4 weeks elapsed since a missed scheduled clinic appointment or refill in the prior 2 years). c. Failed to link to HIV care despite ≥3 months elapsed since HIV diagnosis
**6.**	Females: human chorionic gonadotrophin (HCG) negative and willing to use one highly effective form of contraception if WORP
**7.**	Male participants are advised to wear a condom for sexual intercourse.
**8.**	Must sign informed consent form (ICF) indicating that the participant understands the purpose of, and procedures required for, the study and is willing to participate in the study.
**9.**	Willing and able to attend all clinic appointments.
Exclusion Criteria	
**1.**	Not virologically suppressed (VL <200 c/mL) for >3 months at the conclusion of screening process.
**2.**	Previous use, or intention to use, protease inhibitor-based ART at any time.
**3.**	Evidence of prior HIV-1 resistance test with NNRTI drug resistance mutations (other than K103N) and/or INSTI drug resistance mutations.

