### Interventions

Screening for eligible participants is performed, and the baseline visit (Day 1) will occur within 4 months of the first screening visit. After participant information is provided an assessment of understanding is performed. Those who understand the implications of the study and are keen to participate are invited to provide written informed consent and are evaluated for eligibility during the screening period. Participants who are viraemic (HIV-1 VL ≥200 copies/mL) at the time of screening must be virologically suppressed on a regimen of 2 NRTIs + DTG for a minimum of 3 months prior to randomization.

Eligible participants are randomly assigned to one of 2 treatment arms using a computer-generated randomization schedule prepared in advance by the trial statistician. To ensure balance, randomization employs randomly permuted blocks of random block sizes (4, 6, 8, 10, 12) and stratified according to the study site. Based on this randomization code, the study investigational product is packaged and labelled.

On Day 1, virologically suppressed (<200 copies/mL for at least 3 months) individuals are randomized 1:1 to either continue daily oral ART (2 NRTI + DTG, control arm), or switch to Q2M CAB LA + RPV LA IM, the intervention arm. Those randomized to the intervention arm are offered either an optional oral lead in (OLI) of 1 month daily oral CAB and RPV or a direct to injection (DTI) approach. This decision to dose with or without an OLI phase is determined by the study participant following the informed consent discussion with the investigator. Baseline assessments are performed on Day 1.

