### Comparator Arm (Oral cART)

Participants take a regimen of 2 NRTIs + DTG as per local country guidelines up to Month 24. If toxicity occurs, participants may switch daily oral ART drugs, but only after prior discussion with the Sponsor.

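### The resistance endpoint counts new INSTI and NNRTI mutations but not NRTI mutations, so it is narrower than its objective and leaves out two of the three oral-arm drugs

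*Protocol article*

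**What the plan says.** The resistance row of Table 3 (Objectives and endpoints) opens with "To assess genotypic viral resistance in participants experiencing protocol-defined CVF". It extends this to "its impact on future treatment options including proportion who resuppress on dolutegravir". CVF is defined there by one threshold for everyone, two consecutive viral loads of at least 200 c/mL, and the row names neither an arm nor a drug class. The single endpoint in the row is the frequency of "emergence of new integrase strand transfer inhibitor (INSTI) and non-nucleoside reverse transcriptase inhibitor (NNRTI) drug resistance mutations" among those who fail, through 12 and 24 months. No other endpoint in Table 3 mentions NRTI mutations.

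The two regimens differ in class:

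- Oral arm (Comparator Arm section): "Participants take a regimen of 2 NRTIs + DTG as per local country guidelines up to Month 24".
- Long-acting arm (Interventions section): "switch to Q2M CAB LA + RPV LA IM, the intervention arm", that is, one INSTI (cabotegravir) and one NNRTI (rilpivirine).

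The footnotes to Table 2 describe reflex resistance testing on stored plasma at "VL ≥200 c/mL in the CAB LA + RPV LA group, or ≥1000 c/mL in the cART group". The testing is not restricted to particular classes. The footnotes also provide for stored baseline cells for archived genotyping.

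**The concern.** An endpoint should be able to answer its objective. Here the objective concerns resistance at failure in general, and its consequence for later treatment, while the endpoint lists two classes. Those two classes are exactly the two drugs of the long-acting regimen. For the oral regimen they cover dolutegravir only. The NNRTI class is counted although the oral regimen contains no NNRTI, and the NRTI class is not counted although it contains two.

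An oral-arm participant who fails with a new NRTI mutation and no new INSTI or NNRTI mutation therefore adds nothing to this endpoint. The long-acting regimen has no matching gap. If the frequencies are set side by side by arm, as a reader of the results is likely to do, they do not measure the same thing. The consequence for later treatment is also described without the class that accompanies dolutegravir in this trial's own oral regimen.

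This is separate from the different viral-load triggers for genotyping in the two arms. It would remain if every failure were genotyped.

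**Working it through.** **Step 1. Set the endpoint against the regimens.**

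| Class | Counted by the endpoint | In long-acting regimen | In oral regimen |
|---|---|---|---|
| INSTI | yes | yes (cabotegravir) | yes (dolutegravir) |
| NNRTI | yes | yes (rilpivirine) | no |
| NRTI | no | no | yes (two drugs) |

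On-regimen classes counted: 2 of 2 in the long-acting arm and 1 of 2 in the oral arm. By drug, that is 2 of 2 and 1 of 3. One qualification applies: long-acting participants who go direct to injection stay on oral ART for the first 4 weeks, so that arm has a short NRTI exposure too.

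**Step 2. Direction.** Leaving out a class can only lower a count. At mutation level, every new NRTI mutation is missed. At participant level, only those with a new NRTI mutation and no new INSTI or NNRTI mutation are missed. On-regimen resistance in the oral arm is therefore under-stated or unchanged, never over-stated.

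**Step 3. Scale.** The plan gives no figure for the resistance endpoint, so there is none to reproduce. The only usable inputs are in the Sample size calculation: 270 per arm, and a "non-inferiority margin of 4% and assumed virologic failures rates of 4% in CAB LA + RPV LA and 6% in daily oral ART". As a check on those inputs:

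- Primary endpoint: n = 2 × 0.78 × 0.22 × (1.960 + 0.842)² / 0.10², which rounds up to 270 per arm, as stated.
- CVF: SE = √[(0.04 × 0.96 + 0.06 × 0.94)/270] = 0.0187. Power = Φ[(0.04 + 0.02)/0.0187 − 1.96] = 89%, consistent with the stated minimum of 80%.

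Expected failures:

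- oral arm: 0.06 × 270 = 16.2
- long-acting arm: 0.04 × 270 = 10.8

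Let f be the share of genotyped oral-arm failures with a new NRTI mutation and no new INSTI or NNRTI mutation. Let g be the share of oral-arm failures that are genotyped. The number missed is 16.2 × g × f. The document gives neither f nor g. The values below are assumptions chosen to show the range.

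| f | g = 1 | g = 0.5 |
|---|---|---|
| 0% | 0 | 0 |
| 10% | 1.6 | 0.8 |
| 25% | 4.1 | 2.0 |
| 50% | 8.1 | 4.1 |

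g may be below 1 because reflex testing in the oral arm starts at 1000 c/mL while CVF starts at 200 c/mL, so failures at 200–999 c/mL may have no genotype. The footnote refers to a section of the full protocol, not shown, that gives an alternative threshold for this arm.

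**Step 4. Time frame.** The 4% and 6% rates belong to the key secondary analysis, which is at Month 12. The resistance endpoint also runs through Month 24, for which the article assumes no failure rate. The counts above are therefore a Month 12 scale only.

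**The case against.** The strongest reply is that the class choice is deliberate and coherent. INSTI and NNRTI are the classes put at risk by the switch. The same pair defines exclusion criterion 3 in Table 1 ("Evidence of prior HIV-1 resistance test with NNRTI drug resistance mutations (other than K103N) and/or INSTI drug resistance mutations"). The one later treatment option named in the objective is dolutegravir, itself an INSTI, and that class is counted in both arms. An oral-arm failure with only an NRTI mutation is correctly reported as having no new INSTI or NNRTI mutation, so nothing reported would be false. The genotypes are not limited by class, so NRTI results probably exist, and listings by class are often left to the analysis plan.

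Much of this stands. The endpoint is a legitimate measure of what it names, and the data are not shown to be lost. What does not follow is that the objective and endpoint agree. The protocol itself lists the classes, so an analysis plan that follows it inherits the gap.

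Three stronger readings are tempting and are not supported:

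- **That a formal comparison is biased against the long-acting arm.** The efficacy, immunology and safety objectives are worded as comparisons with oral ART. The resistance objective is not, and the article's Statistical Analysis Plan section describes no test of it. The one-sided effect concerns descriptive by-arm reading only.
- **That the omitted cases could reverse the direction of the result.** The document gives no resistance count or rate for either arm, so there is no direction to reverse.
- **That the question about later treatment goes unanswered for oral ART.** INSTI mutations, which bear on the dolutegravir option it names, are counted in that arm. The answer is partial.

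**Conclusion.** The point holds as a mismatch between an objective and its only endpoint. All classes of the long-acting regimen are counted, and the NRTI class of the oral regimen is not. A descriptive by-arm reading can only under-state on-regimen resistance in the oral arm, and the consequence for later treatment is only partly described.

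The mismatch follows from the text and rests on no assumption. Its size cannot be derived from the document. With about 16 oral-arm failures at the assumed 6%, it is zero to a few participants for most of the range shown. It reaches about 8 only if half of all failures carried NRTI-only resistance and all were genotyped. Incomplete genotyping at 200–999 c/mL would reduce it.

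The primary endpoint and the key secondary CVF test are untouched. This is an inexpensive improvement to a secondary endpoint and does not threaten the trial's main conclusions.

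**What to change.** In Table 3, define the endpoint as emergence of new INSTI, NNRTI or NRTI resistance mutations in participants with CVF, through 12 and 24 months. Report each class separately and by arm. Keep the present INSTI/NNRTI frequency as one of the reported rows, so that the planned result remains available. Add a descriptive summary of participants with any new mutation to a class in their assigned regimen, giving the number of failures genotyped in each arm as the denominator alongside the number who failed.

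The cost is a change of wording and one added table. No visit or sample is added. NNRTI and NRTI mutations are both read from reverse transcriptase, so the same genotypes supply them, provided that the sequenced region includes the NRTI positions. The stored baseline cells and failure plasma in Table 2 allow new mutations to be separated from earlier ones.

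### The treatment-satisfaction endpoint puts two different measures under one label (HIVTSQs at Month 6, HIVTSQc at Months 12 and 24) and reports only the long-acting arm, although both arms are scheduled for the questionnaire

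*Protocol article*

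**What the plan says.** Table 3 (section Objectives and endpoints) lists an exploratory objective, "To assess treatment satisfaction", with one endpoint: "For participants in the CAB LA + RPV LA group, change from baseline in HIVTSQ scores at Month 6, Month 12 and Month 24". The version of the questionnaire is not named.

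The abbreviations under Table 2 (section Study procedures) distinguish two versions: "HIVTSQc= HIV Treatment Satisfaction Questionnaire- change version; HIVTSQs= HIV Treatment Satisfaction Questionnaire- status version". Each has its own row in the schedule. HIVTSQs is marked at Baseline and Month 6, and HIVTSQc at Months 12 and 24.

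On who completes them, Table 2 applies a general rule: "activities listed below only apply if the participant has a visit scheduled in line with their randomization arm". Where a questionnaire is meant for one arm only, the table can say so, as in "OLI questionnaire (LA arm only". The two HIVTSQ rows carry no such limit. The section Qualitative methods sub-study says that "participants complete questionnaires on quality of life" and on treatment satisfaction at Baseline and Months 6, 12 and 24. It neither restricts this to an arm nor separates the versions. The same section does restrict the treatment-preference question to the long-acting arm.

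**The concern.** A change from baseline is normally the follow-up score minus the baseline score on the same instrument. The endpoint names three times as though one such measure were repeated, but the schedule changes instrument between Month 6 and Month 12. An analyst who follows Table 3 literally has no status score to use after Month 6. One who follows it loosely may put three values in one table or model and read a time course into them, when the step from Month 6 to Month 12 is partly a change of instrument.

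The second issue is the choice of arm. A before-after change in the long-acting arm of an open-label trial cannot separate the regimen from trial participation or from expectations about a new treatment. A randomised comparison for the same questionnaire is already in the schedule, and the endpoint gives it no role.

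**Working it through.** No sample size, power or alpha figure is involved, so there is no stated number to reproduce. The check maps the marks in Table 2 to its column headings and compares them with Table 3.

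**Step 1. Timing of each instrument (Table 2)**

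| Row | Marked at |
|---|---|
| HIVTSQs (status) | Baseline, 6 |
| HIVTSQc (change) | 12, 24 |
| EuroQoL | Baseline, 6, 12, 24 |
| MOS-HIV | Baseline, 6, 12, 24 |

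**Step 2. What can be derived at each stated time.** Write S for the status score and C for the change-version score, with the month as subscript and 0 for Baseline.

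| Time | Status difference | Change-version difference | What exists |
|---|---|---|---|
| Month 6 | S6 − S0: both scheduled | C6 − C0: neither scheduled | S6 − S0 |
| Month 12 | S12 − S0: S12 not scheduled | C12 − C0: C0 not scheduled | C12 alone |
| Month 24 | S24 − S0: S24 not scheduled | C24 − C0: C0 not scheduled | C24 alone |

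A baseline-subtracted score exists at 1 of 3 stated times. At the other 2 there is a single reported change score with no baseline value of its own.

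**Step 3. Is this a misread table?** The EuroQoL and MOS-HIV rows serve as a control. Table 3 asks for their change from baseline at Months 12 and 24, and Table 2 schedules both instruments at Baseline and at those months. These endpoints can be derived as written. Among the questionnaire endpoints of this form, only HIVTSQ lacks the scores that its wording calls for.

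**Step 4. Which arms are scheduled.** From the visit rows of Table 2:

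- Long-acting arm: Baseline, 1, 2, 4, 6, 8, 10, 12, 14, 16, 18, 20, 22, 24.
- Oral arm after screening: Baseline, 3, 6, 9, 12, 15, 18, 21, 24.

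Both lists contain Baseline, 6, 12 and 24. Under the table's general rule, both arms complete HIVTSQs at Baseline and Month 6, and HIVTSQc at Months 12 and 24.

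**Step 5. What the schedule supports.** At Month 6, S6 can be regressed on arm and S0. The arm coefficient is then a randomised between-arm difference adjusted for baseline. At Months 12 and 24, C can be summarised by arm.

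**The case against.** The strongest reply is that the endpoint says HIVTSQ without a suffix, and that HIVTSQc is by name a change version. On that reading, Months 12 and 24 are covered by the change score that participants report directly, and Month 6 by a difference of status scores. This stands as far as it goes. A reader might infer that the endpoint cannot be computed at Months 12 and 24, or that two of three time points are lost. The documents do not support that, because satisfaction data are scheduled at all three times and a rewording makes them reportable. What the reply does not remove is that these are two measures under one label, with no version assigned to each time.

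The reply on the arm restriction is that it is stated openly, for an exploratory objective that names no comparison, and that the preference endpoint beside it is also limited to the long-acting arm. Control participants stay on the type of regimen they were already taking, so describing satisfaction among those who switch can be defended. This also stands: the restriction is a choice and contradicts nothing. A reader might infer that the control-arm responses will go unused. The article does not say so. It describes no analysis method for any exploratory questionnaire, and the statistical analysis plan is not shown. The point is only that a better comparison is available from data already scheduled.

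A reader might also want HIVTSQs added at Months 12 and 24. Enrolment ran from 6 January 2023 to 6 May 2024, a spread of 16 months. Adding the form now would reach only later-enrolled participants at visits still to come. It would also need an approved protocol amendment across 7 sites in three countries. The gain does not justify this for an exploratory endpoint.

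**Conclusion.** The point holds as a minor one. Table 3 gives one label to a baseline-subtracted status score at Month 6 and a directly reported change score at Months 12 and 24. Only 1 of the 3 times yields a follow-up minus baseline difference, and the three values should not be pooled or trended. Limiting the endpoint to the long-acting arm is permissible. It is nonetheless weaker than the randomised comparison that the schedule supports.

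This rests on Table 2 having been extracted correctly, which the EuroQoL and MOS-HIV rows support, and on the HIVTSQ rows applying to both arms, as the table's rule and the text indicate. The article does not state what reference point the change version asks about. It also does not state whether the baseline form is completed before allocation is known, since randomisation and baseline assessments both fall on Day 1. The baseline adjustment is cleanest if it is.

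The endpoint has no role in the stated hypotheses, significance levels or sample size. The primary and key secondary analyses are unaffected.

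**What to change.** 1. Replace the single entry in Table 3 with two exploratory endpoints: change from baseline in HIVTSQs at Month 6; and, separately, HIVTSQc score at Months 12 and 24. State that the two are not combined or shown as one time course.
2. Analyse Month 6 HIVTSQs as a between-arm difference adjusted for baseline HIVTSQs, with a 95% confidence interval. Keep the within-arm change as a description if wanted.
3. Report HIVTSQc at Months 12 and 24 by arm.
4. Make the sentence on satisfaction questionnaires in the Qualitative methods sub-study section say which version is given when, and confirm that both arms complete them.

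The cost is wording and a little extra analysis, with no new visits or questionnaires. The comparison has a limit that should be reported with it: allocation is open, so a between-arm difference in satisfaction still carries expectation effects.
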